### Diagnostic criteria

The diagnostic criteria of IPA are based on the 2008 EORTC/MSG framework [17]. Host factors, clinical criteria and mycological criteria to establish the diagnosis of IPA in this study population are listed in Table 2. In accordance with the study by Prattes et al. [11], URD is added as one of the host factors. We propose to make this modification due to several reasons. Host factors of the diagnostic criteria in previous guidelines were originally defined for haematological patients but have not been validated in non-neutropenic patients. Additionally, those typical host factors promoted by EORTC/MSG are frequently absent in non-haematological patients [2, 23]. Patients will be classified into proven, probable, possible and no IPA groups according to the revised 2008 EORTC/MSG criteria [17] (Table 3).

**Table 2 Tab2:** The diagnostic framework for IPA in patients with URD

Host factors	Recent history of neutropenia (< 0.5 × 10^9^ neutrophils/L for > 10 days) temporally related to the onset of infection Prolonged use of corticosteroids at a mean minimum dose of 0.3 mg/kg/day of prednisone equivalent for > 3 weeks Treatment with immunosuppressants during the past 90 days Inherited severe immunodeficiency Underlying respiratory diseases including chronic pulmonary diseases (COPD, asthma, lung cancer, bronchiectasis, interstitial lung diseases, and cystic fibrosis) and acute pulmonary diseases (bacterial pneumonia, viral pneumonia, and acute bronchitis)
Clinical criteria	The presence of 1 of the following 3 signs on chest computed tomography: Dense, well circumscribed lesion(s) with or without a halo sign Air-crescent sign Cavity on chest computed tomography
Mycological criteria	Cytologic or microscopic evidence of *Aspergillus* elements or recovery of *Aspergillus* in sputum or BALF Positive GM test in serum or BALF

**Table 3 Tab3:** IPA classification according to revised 2008 EORTC/MSG criteria

Proven IPA	Histopathological or cytopathological examination of lung tissue showing *Aspergillus* hyphae from needle aspiration or biopsy specimen with evidence of associated tissue damage, OR positive culture result for *Aspergillus* from a sample obtained by sterile procedure from the lung.
Probable IPA	Host factors, AND clinical criteria, AND mycological criteria
Possible IPA	Host factors AND clinical criteria
No IPA	Other cases excluded from proven, probable and possible IPA groups

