### Statistical analysis

The data will be analysed with SPSS 22.0 software (IBM Corp, Armonk, NY, USA). Two analyses will be performed based on the IPA classification, one in which patients with possible IPA will be excluded in the calculation and a second analysis in which patients with possible IPA will be classified as not having IPA. Therefore, the comparisons and analyses will be (1) proven/probable IPA versus no IPA, and (2) proven/probable IPA versus possible/no IPA [43]. The sensitivity, specificity, negative predictive value (NPV), positive predictive value (PPV), and diagnostic odds ratio, including 95% confidence intervals, will be calculated for different biomarkers. ROC analysis will be performed and AUC (including 95% CI) and cut-off values will be established from the ROC curves for GM, RT-PCR, TAFC and bmGT. The McNemar χ^2^ test will be used to compare sensitivity, specificity, NPV, and PPV between different assays. The difference in hospital stay and the survival between possible or no IPA versus proven or probable IPA will be analysed with chi-square tests, and the relationships between the levels of biomarkers and the hospital stay and survival will be analysed via regression models. *P* < 0.05 will be defined as statistically significant.

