There are concerns about the specificity of the sputum assay related to colonization or contamination. Nevertheless, the four biomarkers (GM, JF5 antigen, TAFC, bmGT) in our study are produced and released during fungal growth. It is less likely that the increase in the levels of these biomarkers is a result of contamination of fungal spores. In addition, lower airway secretions will be used by sputum induction, and sputum quality control by squamous cell counting and viability calculation will further exclude the possibility of contamination. We will also determine an appropriate cut-off value of different sputum biomarkers, which will help to differentiate colonization from infection.

There are several highlights of this study. We systematically evaluate the validity of various biomarkers based on sputum from lower airways for the diagnosis of IPA for the first time; in particular, the establishment of a method that simultaneously detects TAFC and bmGT in sputum is first described and applied for patents and reported. Furthermore, the study population, i.e., patients with URD, has been increasingly recognized to present with IPA, which is associated with high mortality [12], but only has been addressed in a small number of studies. We assess the sputum biomarkers for IPA diagnosis in this population for the first time, and the results may help to provide novel, non-invasive and valuable diagnostic tools for IPA in patients with URD. In addition to sputum, serum and BALF will also be collected and compared for their diagnostic performance. In the statistical analysis, we will conduct two different analyses to investigate the impact of the possible IPA group on the interpretation of the results. Except for the investigation of diagnostic efficacy, we will also conduct a clinical follow-up to observe the prognosis of different types of IPA and further investigate host factors predisposing to IPA in patients with URD.

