This study has some limitations that should be considered. The categories of probable and possible IPA are proposed for immunocompromised patients only in the consensus report by the EORTC/MSG. However, this report recognizes that the revised definition of IPA does not necessarily apply to immunocompetent patients as it is difficult to find a sufficient basis for identifying appropriate host factors. Patients with URD may possess much different risk factors to *Aspergillus* infection compared to those immunocompromised individuals. As in the study by Prattes et al. [11], pre-existing respiratory disease is added as an independent host factor to establish the diagnosis in our study. We will also conduct post hoc analyses of the host factors linked to diagnosis and prognosis for further investigation. The concentration of biomarkers in the sputum may fluctuate with the production and expectoration of the sputum and the releasing of the biomarkers from the infection site. However, this study already includes a great number of biomarkers from different sample types with a comparable large sample size, and we do not perform serial tests for sputum biomarkers at different time points across the disease course, which may lead to the underestimation of the diagnostic performance of several biomarkers. Further study may be warranted to investigate the dynamic variation of different *Aspergillus* biomarkers in sputum.

In conclusion, the design and protocol of a clinical trial that investigates the performance of sputum signatures for the diagnosis and prognosis of IPA in patients with URD are presented here. The results of this innovative study are expected to provide answers to the following questions. Are sputum signatures valuable diagnostic tools for IPA in patients with URD? Which signature is the strongest potential candidate? Would the modified host factors be appropriate for this patient population? What disease course of IPA would present in this population? The study findings will provide evidence and novel insights into these areas, which have not been accessed.

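### The sentence on hospital stay and survival names one contrast, with possible IPA merged into no IPA, although follow-up is meant to show prognosis by type of IPA

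*Protocol article*

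**What the plan says.** All references are to the protocol article.

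- **Diagnostic criteria** sets up four categories: "Patients will be classified into proven, probable, possible and no IPA groups". By Tables 2 and 3, possible IPA needs a host factor and a CT sign; probable IPA needs mycological evidence as well.
- **Statistical analysis** first defines two ways of handling possible IPA, "one in which patients with possible IPA will be excluded in the calculation" and a second that counts it as not IPA. It continues: "Therefore, the comparisons and analyses will be (1) proven/probable IPA versus no IPA, and (2) proven/probable IPA versus possible/no IPA".
- The same section then turns to outcomes: "The difference in hospital stay and the survival between possible or no IPA versus proven or probable IPA will be analysed with chi-square tests". The only other outcome analysis there regresses hospital stay and survival on biomarker level, which is not a comparison by IPA category.
- **Discussion**, in the paragraph on the study's highlights, says "we will conduct two different analyses to investigate the impact of the possible IPA group on the interpretation of the results". It then moves on to follow-up as something beyond diagnostic efficacy: "we will also conduct a clinical follow-up to observe the prognosis of different types of IPA". The closing paragraph lists among the questions to be answered: "What disease course of IPA would present in this population".

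**The concern.** The stated purpose of follow-up and the stated analysis do not match. Prognosis by type of IPA needs outcomes for proven, probable and possible IPA to be visible separately. The named contrast pools proven with probable on one side and possible with none on the other.

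The pooling also affects what the test means. Its null hypothesis is that proven/probable patients fare the same as a mixture of patients with a suspicious CT and patients without one. If some possible cases are true IPA, their deaths and long stays count on the non-IPA side, and the contrast moves towards zero. A real difference in outcome could then be missed or understated.

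**Working it through.** **1. What each planned analysis can show**

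| Analysis in Statistical analysis | Possible IPA is | Separates proven, probable and possible? |
|---|---|---|
| Classification 1 (general sentence) | left out | No |
| Classification 2 (general sentence) | pooled with no IPA | No |
| Outcome sentence | pooled with no IPA | No |
| Biomarker regression | not a factor | No |

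The aim of showing prognosis by type is therefore unmet by the named analyses, whether or not classification 1 is meant to extend to outcomes.

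**2. Is excess risk in possible IPA plausible?** Underlying respiratory disease is both an inclusion criterion and a host factor in Table 2, so every participant meets the host-factor condition. Possible IPA then differs from probable IPA only in lacking mycological evidence. The article itself calls culture insensitive (Background) and puts serum GM sensitivity at 23.1–42% in non-haematological patients (Discussion). Some missed mycology is to be expected. On the other side, lung cancer and bacterial pneumonia are eligible conditions, so a CT sign without mycology need not be IPA.

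**3. The plan's own figure.** The article gives no sample size or power for outcomes. Its 59 per group comes from AUC precision: a = 1.414 × Φ⁻¹(0.795) = 1.165; V = 0.0099 × exp(−a²/2) × (6a² + 16) = 0.1213; n = 1.96² × 0.1213 / 0.09² = 57.5, so 58. That is within one of the stated 59, and the small gap has no bearing here. I use 59 per group.

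**4. Size of the dilution.** These inputs are assumptions, since the documents give none of them: mortality 40% in proven/probable IPA and 15% in no IPA; m = 20, 40 or 59 possible cases; possible-IPA mortality p at the no-IPA level (15%), midway (27.5%) or at the full level (40%).

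Merged comparator risk = (59 × 0.15 + m × p) / (59 + m). For m = 40 and p = 0.40 this is (8.85 + 16) / 99 = 25.1%, so the difference is 40 − 25.1 = 14.9 points.

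Power is from 200,000 simulated trials per scenario, using an uncorrected two-proportion chi-square test at 0.05. A normal approximation agrees to within about one point.

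| Possible-IPA mortality | m = 20 | m = 40 | m = 59 |
|---|---|---|---|
| Excluded (reference) | 25 points, 88% | 25 points, 88% | 25 points, 88% |
| 15% | 25 points, 92% | 25 points, 94% | 25 points, 96% |
| 27.5% | 21.8 points, 82% | 20.0 points, 78% | 18.8 points, 75% |
| 40% | 18.7 points, 67% | 14.9 points, 51% | 12.5 points, 39% |

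**5. Other assumed rates, with m = 15, 30 and 59.**
- 50% against 20%: power is 94% with possible IPA excluded; 90%, 88% and 84% merged at intermediate risk; 82%, 69% and 48% at full risk; 96–98% at the no-IPA risk.
- 40% against 20%: power is 66% excluded; 61%, 58% and 54% at intermediate risk; 51%, 40% and 27% at full risk; 72–80% at the no-IPA risk.

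The pattern is the same. The calculation covers mortality only. Length of stay would be diluted in the same direction, but I have not sized it.

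**The case against.** Four points on the other side carry weight.

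- **The general sentence may already cover outcomes.** It comes before any endpoint is named and is not limited to accuracy. A reader might infer from the outcome sentence that the merged contrast is the only one planned; the text does not establish that. It is ambiguous, because the outcome sentence repeats one version and the Discussion introduces follow-up separately from diagnostic efficacy.
- **Descriptive tables may exist elsewhere.** Survival and hospital days are collected in follow-up and everyone is classified, so a full protocol or analysis plan could report outcomes by category. A reader might infer that the course of possible IPA will never be shown; a condensed article cannot support that. What stands is that the contrast the article chose to name does not serve the aim the article states.
- **The power loss is conditional, and its sign is not fixed.** A reader might quote the largest loss, 49 points. That needs 59 possible cases, all at full IPA-level mortality, and the documents support neither figure. The trial is sized on AUC precision and claims no power for outcomes, so loss of power carries limited weight.
- **Excluding possible IPA is not clean either.** A reader might infer that it should be the main contrast. Under Participants screening and recruitment, patients without the CT criteria become no IPA. That contrast therefore sets CT-positive against CT-negative patients and mixes IPA with having a lung lesion. The merged comparator keeps CT-positive patients who lack mycology. Neither contrast dominates.

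**Conclusion.** The mismatch is real and does not depend on any assumed number: neither two-group classification can show prognosis by type of IPA, and the outcome sentence names only the merged one.

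The dilution is a conditional addition. It arises only if possible IPA carries excess risk, which is plausible from the article's own definitions but not shown. Under 40% against 15% mortality, 59 per group and 20 to 59 possible cases, merging costs about 6 to 13 points of power at intermediate risk and about 21 to 49 at full risk, and gains 4 to 8 if there is no excess risk. These figures show a range of consequences and do not predict this trial. The point concerns a secondary aim and leaves the accuracy analyses untouched, but it is worth correcting because the correction is so cheap.

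**What to change.** In Statistical analysis, amend the outcome sentence to say that hospital stay and survival will be compared under both classifications already defined there: possible IPA excluded, and possible IPA merged with no IPA. Do not rank one as main. Add that survival and hospital stay will be reported separately for proven, probable, possible and no IPA.

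The cost is one repeated analysis and one descriptive table on data already collected at the 3- and 6-month reviews. The write-up should note that the possible-excluded contrast compares CT-positive with CT-negative patients. Some categories, proven IPA in particular, may be small, so the table should be descriptive and not a further set of tests.

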## Background

Invasive pulmonary aspergillosis (IPA) is a fungal infection that occurs primarily in patients with severe immunodeficiency [1]. In recent years, IPA has been increasingly recognized in patients without haematologic malignancy or organ transplantation [2–9], especially in those with underlying respiratory diseases (URD) [2–5, 10–12]. Remarkably, the mortality rate among non-neutropenic patients was significantly higher than that in neutropenic patients [12], such that a mortality rate of greater than 90% in patients with chronic obstructive pulmonary disease was reported [13].

Although a favourable clinical outcome of patients with IPA is largely influenced by the initiation of effective antifungal treatment [14], the early diagnosis of IPA is still notoriously difficult, and few diagnostic tools are available [15]. The “gold standard” to confirm the diagnosis is the histopathological examination of lung tissue obtained by thoracoscopic or open-lung biopsy [16]. Considering its limitation in terms of feasibility and sensitivity in clinical practice, the European Organization for Research and Treatment of Cancer/Mycoses Study Group (EORTC/MSG) proposed diagnostic criteria for IPA that integrate host factors, clinical evidence and mycological findings [17]. However, the diagnosis of IPA in patients with URD remains challenging. The host factors defined by the EORTC/MSG framework do not necessarily apply to patients in the respiratory wards or intensive care units [2], and the official group recognized this as “an omission” [17].

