### Clinical follow-up

Patients will receive telephone reviews at 3 months and 6 months after enrolment. Information that includes the patients’ symptoms, days of hospitalization and survival will be recorded and checked in the medical record system.

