### Sample size calculation

GM is the most studied biomarker for the diagnosis of IPA among our candidate signatures; therefore, the sample size calculation is based on the diagnostic accuracy of the sputum GM assay reported by previous studies. Receiver operating characteristics (ROC) curves show the trade-off between sensitivity and specificity, and the area under the curve (AUC) is considered as an overall index of accuracy for quantitative biomarkers. The sample size estimation is based on AUC reported previously [27].

With 95% confidence (*α* = 0.05) to guarantee the marginal error of estimate (i.e. the difference between true AUC and its estimate) does not exceed from a pre-determined value of d = 0.09, and expecting an equal number of diseased and non-diseased cases, the required sample size for each group is:1$$ \mathrm{n}=\frac{{\mathrm{z}}_{\frac{\alpha }{2}}^2\ \mathrm{V}\left(\hat{\mathrm{AUC}}\right)}{d^2} $$

V($$ \widehat{\mathrm{AUC}} $$) denotes the variance of $$ \widehat{\mathrm{AUC}} $$ that is estimated parametrically based on binormal assumption [41, 42]. This binormal assumption is chosen because our study implements a four-category rating scheme (i.e. proven IPA, probable IPA, possible IPA and no IPA). $$ \mathrm{V}\left(\widehat{\mathrm{AUC}}\right) $$ is calculated as follows:2$$ \mathrm{V}\left(\widehat{\mathrm{AUC}}\right)=\left(0.0099\times {e}^{\raisebox{1ex}{$-{a}^2$}\!\left/ \!\raisebox{-1ex}{$2$}\right.}\right)\times \left(6{a}^2+16\right) $$

where a = *φ*^−1^(AUC) × 1.414 and *φ*^−1^ is the inverse of standard cumulative normal distribution. With a pre-specified AUC of 0.795 according to Kimura et al. [27], the required sample size for each group is 59 after above calculation. Therefore, we will recruit a minimum number of 118 participants with 59 controls (no IPA) and 59 cases (proven or probable IPA).

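### Hospital stay is recorded in days but compared with a chi-square test, with no categories defined; the survival test needs a named time point or a log-rank analysis

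*Protocol article*

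**What the plan says.** The Statistical analysis section of the protocol article gives one method for two outcomes: "The difference in hospital stay and the survival between possible or no IPA versus proven or probable IPA will be analysed with chi-square tests".

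The Clinical follow-up section describes the data. "Patients will receive telephone reviews at 3 months and 6 months after enrolment", and "days of hospitalization and survival will be recorded and checked in the medical record system". Stay is therefore a count of days. No grouping of days appears anywhere in the article, and it does not say how a stay that ends in death is counted. Survival is not defined further: the article does not say whether it means vital status at one of the two contacts or time to death.

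The same section adds that "the relationships between the levels of biomarkers and the hospital stay and survival will be analysed via regression models". That sentence concerns biomarker levels, not the comparison between diagnostic groups, so it does not supply another method for the latter.

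**The concern.** A chi-square test compares frequencies across categories. Applied to days, it leaves two options. One is to treat every distinct day value as its own category, which gives a very sparse table and ignores the order of the values. The other is to cut the days at some point. The article fixes no cut, so it could be chosen after the data are seen, and any cut discards information.

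A second matter belongs to the endpoint rather than the test. A patient who dies early in hospital has a short stay, so a group with more early deaths can look better on raw stay.

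For survival, the question is whether chi-square is acceptable when the plan names no time point and some patients may be followed only in part.

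At stake is the comparison of disease course between proven/probable IPA and the rest. The Discussion lists prognosis and disease course among the questions the study should answer, and this is the only between-group comparison of outcome that the Statistical analysis section names.

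**Working it through.** **1. The plan's own figure.** The only sample-size figure rests on the AUC: "With a pre-specified AUC of 0.795" and a margin of error that "does not exceed from a pre-determined value of d = 0.09".
- a = probit(0.795) × 1.414 = 1.165
- V = 0.0099 × exp(−a²/2) × (6a² + 16) = 0.1213
- n = 1.96² × 0.1213 / 0.09² = 57.5, rounded up to 58 per group, against 59 stated

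This reproduces to within one patient per group. Stay and survival do not enter it, and the article gives no effect size or power for either, so everything below rests on assumptions.

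**2. Hospital stay, effect size varied.** Inputs from the article: 59 cases and 59 controls, significance level 0.05. Assumed: lognormal stay rounded up to whole days, median 14 days in the comparator, log-SD 0.8, no deaths. 3,000 simulated trials per row.

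| Ratio of medians | Rank test | Chi-square, median split | Chi-square, raw days |
|---|---|---|---|
| 1.0 (type I error) | 4.8% | 4.9% | 0.9% |
| 1.3 | 42% | 32% | 1% |
| 1.5 | 76% | 61% | 3% |
| 1.7 | 93% | 83% | 4% |

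In the raw-days table about 99% of cells have an expected count below 5. The median split keeps its type I error but costs about 9 to 15 points of power.

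**3. Hospital stay, spread and group size varied.** The comparator in this analysis is possible plus no IPA, whereas the 59 controls in the sample-size section are no IPA only. The comparator may therefore be larger. Taking 59 v 59 and 59 v 90 (31 possible-IPA patients added, assumed), ratio 1.5 and log-SD 0.6 to 1.0:
- rank test: 57–97%
- chi-square on a median split: 45–89%
- chi-square on raw days: 0.4–24%

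Within a scenario, the split loses about 8 to 17 points against the rank test.

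**4. Effect of death on raw stay.** Assumed: 59 per group, median time to live discharge 14 days in the comparator and 1.5 times that in IPA, log-SD 0.8, constant death hazards, about 9% in-hospital death in the comparator.

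| In-hospital death in IPA | Median stay, IPA v comparator (days) |
|---|---|
| 38% | 15.0 v 13.2 |
| 57% | 11.4 v 13.2 |
| 69% | 9.0 v 13.3 |

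The true prolongation is mostly hidden at 38% and reversed from about 57%. At 69% the median-split chi-square is significant in the wrong direction in 55% of trials. A rank test on raw stay is exposed to the same distortion, because the data being ranked are already shortened.

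**5. Survival with loss unrelated to group.** Assumed: exponential survival to 6 months, 59 per group, 2,000 trials per scenario, patients of unknown status dropped from the chi-square test.

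| 6-month mortality | Loss | Log-rank | Chi-square |
|---|---|---|---|
| 20% v 45% | none | 84% | 84% |
| 20% v 45% | 15% | 81% | 80% |
| 30% v 60% | none | 92% | 91% |
| 30% v 60% | 15% | 91% | 89% |

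With equal mortality of 20%, type I error is 5.2–5.7% for chi-square and 5.2–5.4% for log-rank. The two tests are practically equivalent here.

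**6. Survival with unequal loss.**
- True mortality 40% in both groups, about 4% v 32% lost (assumed): type I error is 11.5% if lost patients count as alive, 10.0% if they are dropped, and 4.6% for log-rank.
- True mortality 30% v 60%, about 4% v 20% lost (assumed): power is 71% if the lost count as alive, against 90% for log-rank.

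**The case against.** Several stronger readings are tempting, and the document does not support them.

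*Chi-square is the wrong method for survival too.* A reader might infer this because survival is usually analysed as time to event. The article never defines it so. It sets contacts at two fixed times, and alive or dead at a named contact is a binary outcome for which chi-square is valid. Step 5 shows no material loss. Bias needs loss that differs between groups, as in step 6; the article gives no loss rate, and rules for lost patients are commonly left to an analysis plan. Log-rank itself assumes that censoring is uninformative.

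*Chi-square makes the stay comparison reverse.* Reversal comes from how the endpoint treats death. A Mann-Whitney test on raw days would reverse as well, and in step 4 it takes about 57% in-hospital death in the IPA group.

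*Mortality in this trial will be so high that the distortion must be large.* The Background does say that "a mortality rate of greater than 90% in patients with chronic obstructive pulmonary disease was reported". But this is a report from another study, with no time frame and not stated as in-hospital death. It concerns one of many conditions enrolled here, among them asthma and acute bronchitis, and it is not a design input.

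It is also fair to say that an unseen analysis plan might define categories for stay. Even then, grouping a count of days would remain a poor choice, and the article fixes the test without them. The objection on stay therefore does not remove the point. It limits the survival part and the severity.

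**Conclusion.** The point holds for hospital stay. A variable recorded in days is assigned a test for categories that are not defined. Applied to raw days, the test has little power (at most 24% in the scenarios tried, and 1–4% at 59 v 59 with log-SD 0.8). Applied after a median split, it loses roughly 8 to 17 points against a rank test at a ratio of 1.5. These sizes depend on the assumed lognormal shape, ratio, log-SD and group sizes, none of which the article gives. Separately, raw stay is shortened by in-hospital death, so changing the test alone is not enough.

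For survival there is no error in the method as such. The weakness is that no time point is named and the test cannot use partial follow-up. Log-rank is a refinement that protects against unequal loss.

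Severity: should be fixed. This is a secondary prognostic analysis. The diagnostic accuracy objective and the sample size stand as they are.

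**What to change.** **Hospital stay.** Replace the chi-square test by one of:
- a Mann-Whitney test on days alive and out of hospital to 6 months, with no days counted after death;
- cumulative incidence of live discharge, with death as a competing event.

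Either way, state how in-hospital deaths enter.

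**Survival.** Preferably use Kaplan-Meier curves with a log-rank test to 6 months, censoring at last contact, so that patients with partial follow-up are neither dropped nor counted as alive. If chi-square is kept, name the time point and restrict it to vital status with complete follow-up at that time.

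**Cost.** Wording in the analysis section and no change to sample size. Mann-Whitney, Kaplan-Meier and log-rank are standard procedures in the package the plan already names. The small burden is data extraction: dates of death, discharge and last contact are needed, while the Clinical follow-up section mentions only days of hospitalisation and survival. Deaths after discharge may be known only from the telephone reviews, so the date should be asked for there. The change should be made before outcome data are analysed.

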## Methods/design

### Study design

This is a prospective diagnostic trial. The study protocol has been registered with the Chinese Clinical Trial Registry (ChiCTR-DPD-16009070). Participants will be enrolled from respiratory wards and intensive care units in the West China Hospital, Sichuan University of China. Inclusion criteria are patients (1) with URD including chronic pulmonary diseases (COPD, asthma, lung cancer, bronchiectasis, interstitial lung diseases, and cystic fibrosis) and acute pulmonary diseases (bacterial pneumonia, viral pneumonia, and acute bronchitis); (2) willing to provide informed consent; and (3) able to tolerate sputum induction. Exclusion criteria are patients (1) with underlying haematological malignancies; or (2) that are previous receipts of solid organ transplant; or (3) that are unable to produce sputum.

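### Survival and hospital stay are compared between IPA groups with an unadjusted chi-square test, so a crude difference may partly reflect case mix

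*Protocol article*

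**What the plan says.** The Statistical analysis section names one method for comparing outcome between IPA groups: "The difference in hospital stay and the survival between possible or no IPA versus proven or probable IPA will be analysed with chi-square tests". It names no covariate or stratification factor. The section closes with a general rule that P < 0.05 "will be defined as statistically significant".

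The same sentence also plans regression, but for a different question: "the relationships between the levels of biomarkers and the hospital stay and survival will be analysed via regression models". The exposure there is the biomarker level, not the IPA group.

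On who is compared, the Study design section admits patients "with URD including chronic pulmonary diseases (COPD, asthma, lung cancer, bronchiectasis, interstitial lung diseases, and cystic fibrosis) and acute pulmonary diseases", the acute group being bacterial pneumonia, viral pneumonia and acute bronchitis. On setting it says: "Participants will be enrolled from respiratory wards and intensive care units". Under Diagnostic criteria, "URD is added as one of the host factors". Clinical follow-up is by telephone at 3 and 6 months, with days in hospital and survival recorded.

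On purpose, the Discussion says "we will also conduct a clinical follow-up to observe the prognosis of different types of IPA". Its conclusion lists the disease course of IPA in this population among the questions to be answered. Its limitations paragraph adds post hoc work on host factors related to diagnosis and prognosis, with no method given.

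**The concern.** IPA class is observed, not assigned. The cohort runs from acute bronchitis to lung cancer and from ward to ICU, and these features can be expected to affect both survival and length of stay. If their mix differs between the groups, the crude test measures IPA and case mix together. A significant result could then be taken as the prognosis of IPA.

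The choice of test adds a second problem. Chi-square compares proportions. For survival it discards the time of death and has no place for a patient lost between the two telephone reviews. For days in hospital it cannot be applied until the days are cut into categories, and the article gives no cut points.

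This is more than a covariate list left to a fuller plan. The article fixes a specific test, and an analysis that follows the text would yield a crude answer.

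**Working it through.** **The plan's own figure.** The only numerical target is the sample size, which is based on AUC precision. With AUC = 0.795, a = φ⁻¹(0.795) × 1.414 = 1.165. V = 0.0099 × exp(−a²/2) × (6a² + 16) = 0.1213. n = 1.96² × 0.1213 / 0.09² = 57.5, so 58 per group against 59 stated. This agrees to within one patient and has no bearing on the outcome comparison, for which the article states no figure.

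**How the groups are formed** (Diagnostic criteria, Tables 2 and 3; Participants screening and recruitment):

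- Every participant has a URD and so meets the host criterion. Having a URD does not separate the groups.
- Patients without the CT signs (dense well-circumscribed lesion, air-crescent, cavity) are no IPA.
- Patients with the signs are divided into proven, probable and possible by histology or sterile culture, and then by mycology.
- The comparator is possible plus no IPA, so patients with CT signs stand on both sides of the comparison.

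All proven and probable cases have a CT sign, but only part of the comparator does. If some underlying diseases show such signs more often than others, disease type will be unbalanced. That condition is clinical inference and is not stated in the article.

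**Size, on assumed figures.** All mortality rates and disease shares below are assumptions, and there is no IPA effect. Group mortality = share × high-risk mortality + (1 − share) × low-risk mortality.

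First, assume 6-month mortality of 30% in lung cancer and 5% otherwise:

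| Lung cancer, cases v comparator | Mortality | Ratio |
|---|---|---|
| 40% v 10% | 15.0% v 7.5% | 2.0 |
| 30% v 10% | 12.5% v 7.5% | 1.67 |
| 50% v 20% | 17.5% v 10.0% | 1.75 |
| equal shares | equal | 1.0 |
| 10% v 40% | 7.5% v 15.0% | 0.5 |

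The last row shows that imbalance in the other direction would hide a true difference.

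Second, the chance that the crude test is significant, with n = 59 per group and two-sided 0.05:

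Φ{ [ |p₁ − p₂| − 1.96 √(2p̄(1 − p̄)/n) ] / √[ (p₁(1 − p₁) + p₂(1 − p₂))/n ] }

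| High-risk share | Stratum mortality 5% / 30% | 10% / 40% | 10% / 50% |
|---|---|---|---|
| 50% v 50% | 5% | 5% | 5% |
| 60% v 40% | 10.6% | 11.3% | 15.5% |
| 70% v 30% | 29.6% | 32.3% | 47.4% |
| 80% v 20% | 57.5% | 62.0% | 82.0% |

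One cell in full, for 70% v 30% with 5% / 30%: p₁ = 0.225, p₂ = 0.125, p̄ = 0.175. Then (0.100 − 1.96 × 0.0700) / 0.0694 = −0.535, and Φ(−0.535) = 0.296.

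The 59 per group is itself a simplification. The sample size section counts 59 no-IPA controls, and possible-IPA patients would be added to the comparator here in a number the article does not give.

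**The case against.** A reader might infer that the groups differ by construction in underlying disease. The documents do not support that. Every participant has a URD, and the groups are separated by CT, histology or sterile culture, and mycology. The recruitment section also asks for newly developed CT abnormalities, which limits the role of old lesions, and possible-IPA patients with CT signs sit in the comparator. Imbalance is plausible but not built in.

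A reader might also infer that the plan sets out to attribute deaths to IPA. It does not say so. Its wording is about observing prognosis and disease course, and a crude comparison can serve a purely descriptive aim. This stands, and it is why labelling the comparison descriptive is an acceptable minimum. A significance test between the groups still invites more than description.

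The planned post hoc work on host factors shows that underlying disease in relation to prognosis has been considered. With no method, and no link to the group comparison, it does not replace adjustment.

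The size is assumed, and the first illustration may not reach significance. At 15.0% v 7.5% about 9 v 4 deaths are expected, giving an uncorrected chi-square of about 2.2 and p of about 0.14. That is the expected table only. By the formula above, (0.075 − 1.96 × 0.0582) / 0.0578 = −0.68, so the chance of significance is still about 25% instead of 5%.

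Finally, those 13 deaths would be thin for a Cox model with five parameters (13/5 = 2.6 per parameter). The count comes from a low-mortality illustration. At 38% v 22% there would be 59 × 0.60 = 35 deaths, or about 7 per parameter. The warning stands, and it calls for a small or penalised model.

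**Conclusion.** The concern holds in a limited form. The only stated IPA-group comparison of survival and stay is an unadjusted chi-square test at P < 0.05 in a non-randomised cohort with a wide range of disease and care settings. A crude difference may partly reflect case mix, and the test does not suit time to death or days in hospital.

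The size cannot be derived from the documents. On the assumed figures it runs from no distortion under balance, through about 11% to 16% false significance at a 60% v 40% imbalance, to 30% to 47% at 70% v 30% and higher beyond that. These results assume two risk strata, no IPA effect and 59 per group.

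The comparison is secondary in a diagnostic accuracy study sized on AUC. Sensitivity, specificity, predictive values and ROC results do not depend on it. Priority is low to moderate.

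**What to change.** In the Statistical analysis section:

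- Report crude survival and hospital stay by IPA group as descriptive.
- Make the main secondary comparison a Cox model for survival from enrolment to 6 months, and a regression for length of stay. Each contains IPA group plus a small prespecified set: age, URD category (lung cancer, other chronic, acute), and ICU versus ward at enrolment.
- State in advance that the model will be penalised or reduced if deaths are few.
- If adjustment is not feasible, label the comparison descriptive and do not attribute the difference to IPA.

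The cost is analysis wording and somewhat wider intervals. The covariates are known at enrolment, so no extra patients, visits or samples are needed. The Cox model does need the date of death or last contact, which should be recorded at the planned telephone reviews or from the medical record. Adjustment on so short a list will not remove all differences in severity, and the report should say so.
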